### Provisions for post-trial care {30}

Due to the nature of the study, no post-trial arrangements are required.

### Outcomes {12}

The primary endpoint will be the change in LDL-cholesterol levels from baseline. Key secondary endpoints will include changes in total cholesterol and glycemic profile, circulating levels of adipokines, inflammatory markers, oxidative stress, markers of endothelial and intestinal permeability, microbiota composition, and short-chain fatty acids (SCFAs) values after 3-month dietary intervention vs. baseline. Additionally, the study will investigate the impact of interventions on environmental constraints, such as food waste and metabolic food waste. LDL-cholesterol will be measured as a unique and established quantitative primary outcome, while the assessment of anthropometric parameters, body composition, biochemical profile, SCFAs, and gut microbiota will provide information on the cardiometabolic status of participants. The metric used for analysis will be the change in mean values from the beginning to the end of each 3-month dietary intervention.

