**Methods:**

Fifty clinically healthy individuals showing overweight and presenting a low-to-moderate cardiovascular risk profile will be recruited for a 7-month randomized, open, cross-over dietary trial. Eligible participants will be randomly assigned to a 3-month high-UPF MD (intervention group) or a low-UPF MD (control group), with a 1-month wash-out period. Both intervention diets will have identical food group compositions, with the intervention group consuming 5 servings/day of selected UPF items, and the control group consuming raw/minimally processed items from the same food group. Blood, urine, and fecal samples, alongside food/lifestyle diaries, will be collected from each participant before and after the dietary interventions. The primary endpoint will be the change in plasma LDL-cholesterol levels from baseline. Additional markers include blood pressure, anthropometric parameters, chemical parameters, glucose and lipid-related metabolic markers, incretins, inflammatory and oxidative stress markers, fecal microbiota composition, and short-chain fatty acids. Finally, food waste production will be evaluated through specific validated food diaries. The study has been approved by the Ethical Committee of the University of Milan and the Tuscany Regional Ethics Committee of the Azienda Ospedaliera Universitaria (AOU) - Careggi, Florence.

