## Statistical methods

### Statistical methods for primary and secondary outcomes {20a}

Statistical analyses will be performed using SPSS software for Macintosh (SPSS Inc., Chicago, IL, USA). A *P* value < 0.05 will be considered statistically significant. Data will be analyzed using intention-to-treat and on-treat procedures. The primary outcome (change in body weight) will be analyzed within each group using Student’s *t*-test for paired data. The difference in absolute change (mean value at baseline subtracted from the mean value after the intervention for each subject) will be estimated using the Student’s *t*-test for independent data. Evaluation of distributions and checking for outliers will be performed using histograms and box plots. If appropriate, variables will be logarithmized to normalize the distributions of data. Continuous variables that follow a normal distribution will be summarized using the mean and standard deviations. Categorical variables will be presented in terms of frequencies and percentages. After testing the regression assumption, a general linear model for repeated measurements with adjustments for possible confounding factors will be run to compare the effects of different interventions. Data for the general linear model will be reported as geometric means and 95% confidence intervals. The same analyses will be performed for secondary outcomes. Microbial alpha (richness, Simpson’s, Gini-Simpson’s, inverse Simpson and Shannon’s indices, evenness and dominance) and beta (weighted UniFrac and Bray–Curtis dissimilarity) diversity measures will be assessed using QIIME (v. 1.9).

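### Unadjusted change from each period's own baseline costs precision in this cross-over and is exposed to fading carry-over, and the unconditional promise of geometric means does not fit an absolute-change metric

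*Protocol article*

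**What the plan says.** The trial is a two-arm cross-over with two 3-month diets "with a 1-month wash-out period" between them. Participant timeline {13} puts the visits at months 0 (T0), 3 (T1), 4 (T2) and 7 (T3). T2 is therefore both the end of wash-out and the baseline of period 2.

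On the endpoint, Outcomes {12} says: "The primary endpoint will be the change in LDL-cholesterol levels from baseline". On the metric it says: "The metric used for analysis will be the change in mean values from the beginning to the end of each 3-month dietary intervention".

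Statistical methods {20a} carries the metric into the tests. After a paired t-test within each group, the between-diet step is: "The difference in absolute change (mean value at baseline subtracted from the mean value after the intervention for each subject", compared with an independent-samples t-test. A further step follows: "a general linear model for repeated measurements with adjustments for possible confounding factors will be run to compare the effects of different interventions". Neither the response of that model nor a period baseline among its covariates is named. On scale, the section says "If appropriate, variables will be logarithmized to normalize the distributions of data" and then, without condition, "Data for the general linear model will be reported as geometric means and 95% confidence intervals". The same analyses are to be used for the secondary outcomes.

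**The concern.** In a cross-over each person already serves as their own control, so the diet contrast can be formed from T1 and T3 alone. Subtracting T0 and T2 with a fixed coefficient of one adds two further noisy LDL-cholesterol values. Unless the baselines predict the end values very well, this adds more noise than it removes. The trial is planned on 38 people, so the loss matters.

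The subtraction also makes the period-2 result depend on T2, one month after the first diet. Any residue of that diet at T2 goes straight into the period-2 change.

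The reporting scale is a separate inconsistency. A geometric mean belongs to a positive quantity analysed on the log scale. Absolute change can be zero or negative, and {20a} does not say that every outcome will be logged.

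**Working it through.** **The plan's own figure.** Sample size {14} gives 38 subjects for a 10% change in LDL-cholesterol, 90% power and alpha 0.05 (two-sided assumed). No SD or correlation is stated, so 38 cannot be reproduced, only solved backwards. With k = 1.960 + 1.282 = 3.242:
- parallel, 19 per arm: SD = 10% × √(19/2)/k ≈ 9.5% of baseline LDL-cholesterol;
- paired, 38 people: SD of differences = 10% × √38/k ≈ 19%.

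The article does not say which was used, or whether the SD was for levels or changes.

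**Variance.** Let P = T1−T3 (end values) and B = T0−T2 (baselines). The contrast of changes is (T1−T0)−(T3−T2) = P−B. Let β be the slope of P on B. If P and B have equal variance V, as in all the patterns below:
- change contrast: Var(P−B) = 2V(1−β);
- baseline-adjusted contrast: Var(P−βB) = V(1−β²);
- ratio: 2(1−β)/(1−β²) = 2/(1+β).

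The correlations are assumptions, because the documents give none:

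| Correlation pattern over months 0, 3, 4, 7 | β | Change / adjusted | Change / unadjusted end value |
|---|---|---|---|
| Equal at all visits | 0 | 2.00 | 2.00 |
| Monthly decay 0.80 | 0.01 | 1.98 | 1.98 |
| Monthly decay 0.90 | 0.12 | 1.79 | 1.77 |
| Monthly decay 0.95 | 0.18 | 1.70 | 1.64 |
| Monthly decay 0.98 | 0.22 | 1.64 | 1.56 |
| Within/between period 0.6/0.5 | 0.20 | 1.67 | 1.60 |
| Within/between period 0.8/0.7 | 0.33 | 1.50 | 1.33 |
| Within/between period 0.8/0.6 | 0.50 | 1.33 | 1.00 |
| Within/between period 0.8/0.5 | 0.60 | 1.25 | 0.80 |

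Faster decay makes β slightly negative, because T1 and T2 are only one month apart. At 0.70 per month, β = −0.06 and the ratio is 2/0.94 ≈ 2.1. The ratio falls towards 1 only as β approaches 1.

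**What this could mean for power.** Suppose the SD behind 38 was that of the adjusted contrast. Power with changes is then Φ(k·√(N/38)/√ratio − 1.96):
- ratio 1.25: 83% at N = 38, 91% at N = 50, with 1.25 × 38 = 47.5, so 48 completers for 90%;
- ratio 2: 63% at N = 38, 75% at N = 50, with 2 × 38 = 76 completers for 90%.

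If the SD was already that of changes, planned power stays at 90% and the loss is forgone precision.

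**Carry-over.** Let τ be the diet effect, λ the fraction of the first diet's effect left at T2, and λ₃ the fraction left at T3. Averaged over the two sequences, the expected estimates are:
- change: τ[1 + (λ−λ₃)/2];
- unadjusted end value: τ[1 − λ₃/2];
- baseline-adjusted end value: τ[1 + (βλ−λ₃)/2].

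Take τ = 8 mg/dL and λ = 0.3 as an illustration (neither is in the documents). If the residue has gone by T3 (λ₃ = 0), change gives 8 × 1.15 = 9.2. Adjusted end values give 8.0 at β = 0, 8.4 at β = 1/3, 8.6 at β = 0.5 and 8.7 at β = 0.6. Simulation agreed (9.2 to 9.3, against 8.1, 8.4, 8.6 and 8.7). If the residue persists in full to T3 (λ₃ = 0.3), change gives 8.0, unadjusted end values 8 × 0.85 = 6.8, and adjusted end values between 6.8 (β = 0) and 7.5 (β = 0.6).

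**Scale.** With a mean change of zero, half of the changes in a symmetric distribution are negative, and the log of a negative number is undefined. A geometric mean of LDL-cholesterol levels, or of the end-to-start ratio, is well defined. The stated metric is neither: it is an absolute difference.

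**The case against.** The strongest reply is that change scores are a valid, unbiased estimator after full wash-out, and that choosing another is a matter of efficiency. That is right. Against unadjusted end values, changes are as precise or better when within-period correlation is well above between-period correlation (ratios 1.00 and 0.80 in the table). The comparison that counts is with the adjusted analysis, where changes were less precise in every pattern tried.

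A second reply is that the general linear model allows adjustment for possible confounders, so the period baseline may be intended, and an analysis plan not shown may say so. Changes analysed with T0−T2 as covariate give exactly the same diet estimate as end values with that covariate. This stands as far as it goes: the word change is harmless if the covariate is there. But what the article does fix is a set of t-tests on absolute change with no covariate, and a baseline value is not an obvious reading of a confounding factor.

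Third, the text does not say that the geometric-mean model is fitted to changes. A repeated-measures model on logged levels at four visits would give proper geometric means. This also stands, so a reader who infers that the promised summaries cannot exist goes further than the text. What remains is that the sentence is unconditional while logging is not. An unlogged model yields arithmetic means, and a model of logged levels is not an analysis of absolute change.

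**Conclusion.** The point holds in a limited form. Unadjusted change from each period's own baseline is a stated method, not a missing detail. It costs roughly 25% to 100% in the variance of the diet contrast compared with baseline-adjusted end values, over the correlation patterns tried.

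Three stronger readings are tempting and are not supported:
- That the variance doubles. Two is the value under equal correlations and close to the top of the range. The documents give no correlations.
- That the estimate is biased. Overstatement by 1+λ/2 needs incomplete wash-out at T2 and a residue that fades by T3. The documents neither state nor exclude this. Carry-over lasting to T3 would instead dilute the end-value contrast.
- That power falls to a particular level. Any such figure needs an SD and a difference in mg/dL that the article does not give, and the SD behind 38 may already be that of changes.

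On scale, Outcomes {12} and Statistical methods {20a} are inconsistent as written and must be reconciled. A separate discrepancy touches the same sentences: {20a} introduces its tests with "The primary outcome (change in body weight) will be analyzed within each group using" a paired t-test, whereas {12} names LDL-cholesterol. The fix below assumes LDL-cholesterol is the primary outcome.

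**What to change.** For the primary between-diet comparison, state that LDL-cholesterol at T1 and T3 is the response, modelled within person in the cross-over model with terms for diet and period, and with the within-person baseline difference T0−T2 as covariate. Report the adjusted diet difference in mg/dL with its 95% CI. The changes from T0 and T2 can stay as descriptive summaries.

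Replace the sentence on geometric means with a conditional one: geometric mean ratios with 95% CIs only for outcomes whose levels, not changes, were log-transformed, and arithmetic mean differences otherwise. Name the response and scale of the general linear model.

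Blood is already drawn at all four visits, so no data collection changes. The analysis spends one degree of freedom on the covariate. Adjustment does not fully protect against carry-over, so the assumption of adequate wash-out should be stated. Both sentences are protocol text, so under section {25} the amendment goes to the Ethics Committee for approval before it is implemented.

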### Participant timeline {13}

The study timeline is depicted in Fig. 2. Before starting the intervention, a 2-week run-in period will be implemented during which participants will be asked to complete a 3-day dietary record. Subsequently, participants will be randomly allocated into two groups: one assigned to the intervention arm and the other to the control arm. There will be four clinical evaluations of the study population: at the beginning (time 0) and at month 3 (T1) of the first dietary intervention, and at month 4 (T2) and month 7 (T3) of the second dietary intervention. At each time point, assessments of anthropometric measurements, body composition, and blood pressure will be made, and blood, stool, and urine samples will be collected.

**Fig. 2 Fig2:**
[figure not shown]
Organization of the intervention study

### Sample size {14}

Sample size calculation is based on the results of a previously published study evaluating the impact of a MD intervention on human health [19]. To detect a 10% change in LDL-cholesterol levels with a statistical power of 90% (beta) and alpha set at 0.05, a randomization of 38 subjects (≥ 19 subjects in each group) is considered necessary. Considering possible dropouts, the number of participants was increased to 25 per group. Dropouts will be incorporated into the intention-to-treat analysis, including all participants initially randomized. In addition, per-protocol analysis will be conducted, focusing on those who successfully complete the study without major deviations.

### Recruitment {15}

Female and male participants will be recruited using advertisements on local media, newspapers, social media, official papers, and websites. We will also recruit from our existing database of participants and friends or relatives of the hospital and university staff.

## Assignment of interventions: allocation

### Sequence generation {16a}

A web-based online randomization procedure, free from adaptive randomization procedures, will be employed to generate the allocation sequence. The random assignment sequence will be conducted and overseen by an investigator who will not be involved in participant recruitment, ensuring an impartial and unbiased sequence generation.

### Concealment mechanism {16b}

The order of assignment will be concealed from the experimenters responsible for participant enrolment or intervention assignment. The group assignment details will be presented on a folded sheet of paper enclosed within a sealed envelope, safeguarding the integrity of the allocation sequence until the point of intervention assignment.

### Implementation {16c}

The allocation sequence for the study will be generated at RU1 and RU2 by an external researcher. Participant enrolment will be carried out by trial staff at both research units. The actual assignment of participants to interventions will be executed by the personnel directly involved in visiting the participants.

## Assignment of interventions: blinding

### Who will be blinded {17a}

Blinding of study participants and nutritionists will not be feasible due to the apparent differences between intervention diets. However, outcome measures, being less susceptible to observer influence, will be objectively assessed. Study personnel involved in participant enrolment, data collection, outcome assessment, and data analysis will be blinded to the treatment assignments. To ensure data integrity, an external researcher, independent of the research team, will enter information into the database.

### Procedure for unblinding if needed {17b}

The design is open label with participants and nutritionists not blinded so unblinding will not occur.

## Data collection and management

### Plans for assessment and collection of outcomes {18a}

Assessment and data collection at baseline and follow-up will be conducted at RU1 and RU2 by trained study staff. Subjects will undergo examination between 7:30 am and 10:30 am following a 12-h fasting period. Initially, participants will receive detailed instructions about the trial’s objectives and methodologies. The standardized baseline assessment for both groups will encompass a questionnaire addressing demographic information, risk factors, comorbidities, and the NOVA Food Frequency questionnaire (NFFQ)—a validated tool for estimating UPF consumption in the Italian population [20]. Participants will complete a 3-day weighted dietary record (two weekdays and one weekend day) to enhance the accuracy of energy and nutrient intake estimation. A dietitian, utilizing specific nutritional software linked to a country-specific food-nutrient database, will retrieve these data.

Anthropometric measurements, including height, weight, and BMI, will be recorded using a stadiometer and a professional weighing scale. Furthermore, measurements of waist and hip circumferences will be taken, with subsequent calculation of the waist-to-hip ratio. Body composition will be assessed using a bioelectrical impedance analyzer. Blood pressure will be measured with a sphygmomanometer. Blood, urine, and fecal samples will be collected at baseline and follow-up visits for subsequent analyses of biochemical, inflammatory, oxidative stress markers, and microbiota-associated markers.

At the conclusion of the visit, intervention diets will be dispensed by trial personnel. All participant sessions will maintain uniformity in duration and content. Nutritionists will be instructed not to express favoritism toward either diet or disclose personal eating habits.

### Plans to promote participant retention and complete follow-up {18b}

Strategies to enhance participant retention and follow-up completion incorporate behavior change methodologies, including self-monitoring, alongside continuous availability of study staff for dietary counseling. Upon study completion, participants will be requested to complete an adherence questionnaire, providing insights into their compliance with assigned diets, modifications made, and encountered difficulties. Adherence to the MD will be assessed using the MEDI-LITE adherence score [21] at baseline and during follow-up visits. Participants achieving ≥ 10 points on a scale ranging from 0 to 18 will be considered adherent [22]. For assessing compliance to UPF consumption, food diaries will be evaluated.

In cases where participants miss scheduled appointments, up to three phone calls and an email will be initiated before considering withdrawal from the study. Participants opting for premature discontinuation will not undergo further clinical and laboratory evaluations. The reasons for withdrawal will be documented for subsequent analysis during result interpretation. The entire study will be discontinued if observed results necessitate premature discontinuation.

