### Criteria for discontinuing or modifying allocated interventions {11b}

Participants may discontinue the intervention or withdraw from the study under the following circumstances: (1) participant’s request; (2) if the investigator determines that a participant’s health is at risk due to adverse events or the development of concomitant illness post-entry into the study.

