### Relevant concomitant care permitted or prohibited during the trial {11d}

During the trial, participants will be requested to advise if they require initiation of cortisone therapies, antidiabetic drugs, or vitamin/mineral supplements, and their continuation in the study will be evaluated accordingly. Additionally, the use of products designed for weight loss will not be permitted. If a participant requires the initiation of any of these products based on a doctor’s recommendation during the intervention period, they will be excluded from the study.

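### Measurement stops when a participant discontinues, so the promised intention-to-treat analysis of everyone randomised would rest on imputed rather than observed LDL values

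*Protocol article*

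**What the plan says.** **Analysis promise.** Sample size {14}: "Dropouts will be incorporated into the intention-to-treat analysis, including all participants initially randomized". The statistical methods section {20a} repeats it: "Data will be analyzed using intention-to-treat and on-treat procedures". A per-protocol analysis of those who finish without major deviations is added.

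**Data collection.** Plans to promote participant retention {18b}: "Participants opting for premature discontinuation will not undergo further clinical and laboratory evaluations". Reasons for withdrawal are recorded.

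**Two events named.** Criteria for discontinuing {11b}: "Participants may discontinue the intervention or withdraw from the study under the following circumstances". A single list of circumstances follows (the participant's request, or a risk to health as judged by the investigator). No separate follow-up rule is attached to either event.

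**Concomitant products.** Section {11d} says of people who need to start cortisone, antidiabetic drugs or supplements that "their continuation in the study will be evaluated accordingly". It then bars weight-loss products, and closes by saying of those who start such products on a doctor's recommendation that "they will be excluded from the study".

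**Test and missing data.** The difference in change between groups "will be estimated using the Student’s *t*-test for independent data". Section {20c} plans a review of the amount and causes of missing data, then extreme-case sensitivity analyses by randomised group. Multiple imputation follows only if those show that conclusions could differ, under an assumption of random missingness.

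**The concern.** An intention-to-treat estimate answers what happens when people are assigned to a diet, whether or not they keep to it. That needs outcomes from people who stop. Here the data-collection rule ends measurement at the point where those outcomes become informative. In an open-label trial lasting 7 months, with meals bought and prepared by participants, someone who gives up a diet but would still attend for a fasting blood sample is a foreseeable case.

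Two things are at stake. First, the result reported as intention-to-treat may in practice describe those who stayed, with the remainder filled in by assumption. Second, the loss cannot be repaired later: a statistical analysis plan can choose a method for missing LDL values, but it cannot recover values that were never collected.

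**Working it through.** **Step 1. What each rule needs and delivers.**

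| Item | Where | Consequence |
|---|---|---|
| All randomised participants analysed | {14}, {20a} | Needs outcomes, or a stated substitute, for dropouts |
| No evaluations after premature discontinuation | {18b} | No later LDL value (nor body weight, which {20a} labels as the primary outcome) |
| t-tests on each subject's change | {20a} | Need a start and an end value for the diet period |
| Extreme-case analyses, then conditional multiple imputation | {20c} | The only stated route for including people without an end value |

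**Step 2. What is lost, by time of stopping.** Visits are at time 0, month 3 (T1), month 4 (T2) and month 7 (T3).

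- Stops before T1: only the time 0 value exists, so there is no change score for either diet.
- Stops after T1 and before T3: the period 1 change (T1 minus time 0) exists and can enter the independent-samples t-test. There is no period 2 change and no within-person contrast between diets.

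**Step 3. The dropout margin in the plan.** The article gives 38 participants as necessary and 50 as the target, without a dropout rate. The implied rate is 1 − 38/50 = 0.24, and 38/(1 − 0.24) = 50, so the plan has room for 12 of 50 without complete outcomes. This is a planning margin, not a forecast of loss. The 38 itself cannot be reproduced because no standard deviation is given, but this point does not depend on it.

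**Step 4. Size of the bias (assumed values, not document figures).** Let m be the fraction lost and k the between-diet effect in those lost, as a fraction of the effect in completers.

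- All-randomised effect ÷ completer effect = (1 − m) + m·k = 1 − m(1 − k)
- Overstatement by the completer estimate = 1/[1 − m(1 − k)] − 1

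| m | k = 0 | k = 0.5 | k = 1 |
|---|---|---|---|
| 10% | 1/0.90 − 1 = 11% | 1/0.95 − 1 = 5% | 0% |
| 24% | 1/0.76 − 1 = 32% | 1/0.88 − 1 = 14% | 0% |

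The ratio does not depend on the size of the LDL effect.

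The same point in SD units: if lost and retained participants differ in the treatment contrast by g SD, the completer estimate shifts by m·g. For g from 0.25 to 1.0 this is 0.025 to 0.10 SD at 10% loss and 0.06 to 0.24 SD at 24% loss.

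**Step 5. What imputation can recover.** With no measurements after discontinuation, imputation under random missingness must borrow from people who stayed under observation, most of whom would be on their diet. It therefore tends to return something near the completer contrast. The data cannot test whether that is right for those who stopped.

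**The case against.** The best defence has four parts.

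1. **Missing outcomes are planned for.** Section {20c} gives a sequence that can include everyone randomised. This stands: a reader might infer that the intention-to-treat analysis is impossible, and the article does not support that. What remains is that imputation is a conditional second step, not part of the primary analysis.

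2. **Poor adherence does not remove anyone.** Adherence is scored at follow-up visits, diaries are reviewed, and a separate per-protocol set exists, so people with deviations can stay in the intention-to-treat set. This also stands. A reader might infer that all who fail to keep to a diet are missing by design, but the rule covers only those who opt to discontinue. The surrounding text on missed appointments and reasons for withdrawal suggests that study withdrawal may be what was meant. If so, the wording should say so, because {11b} separates the two events and no rule covers the person who stops only the diet.

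3. **The concomitant-product text is ambiguous.** The products in its last sentence may be the weight-loss products just mentioned or the whole list. It speaks of leaving the study, not the analysis set. A reader might infer that people who start a drug are deleted from the intention-to-treat analysis. The article does not say that, nor does it say the opposite.

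4. **A journal article condenses a fuller protocol.** This is fair for operational detail. But the rule on stopping measurement is stated outright in the article, so it is not an omission.

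**Conclusion.** The conflict is real and of moderate weight. The article promises an analysis of all randomised participants and states a data-collection rule that withholds the outcomes such an analysis needs. As written, the t-tests would leave out every diet period without an end value. Any all-randomised result would rest on extreme-case values or on imputation under an untestable assumption. The promised analysis is undermined, not made impossible.

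On the assumption that those lost have no between-diet difference, the overstatement is about 11% at 10% loss and about 32% at 24% loss. The second figure takes the whole planning margin as lost and a zero effect in every lost participant, so it is the upper end of this illustration and not a prediction. If lost and retained participants respond alike, there is no bias, only a loss of precision. A reader might also infer that loss will differ between the diets; that is plausible in an open-label trial, but the article gives no figure for it and none is claimed here.

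**What to change.** - **Retention section {18b}.** Distinguish a participant who stops following the diet from one who withdraws from the study. Invite the first to the remaining visits already in the timeline, with at least a fasting LDL sample at the end of the period, and analyse by randomised sequence. Measurement ends only for the second.
- **Criteria section {11b}.** Use the same two terms, so that the follow-up rule for each is clear.
- **Concomitant care {11d}.** Reconcile the sentence under which continuation is assessed with the one under which participants are excluded, and make clear which products each covers. State that such exclusion affects the per-protocol set and not the intention-to-treat set. Care decisions stay with the investigator.
- **Missing data {20c}.** State which missing-data method belongs to the primary analysis, instead of making imputation conditional on a sensitivity result.

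**Cost.** A short amendment and a few planned visits for people off diet. The estimated effect may be smaller. In the extreme illustration (all 12 return, with zero effect) the effect falls to 0.76 of the completer value while the standard error falls to √(38/50) = 0.87 of its value, so the ratio of effect to standard error falls to 0.76/0.872 = 0.87. That is the price of estimating the effect the article says it will estimate.
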